**Cost-benefit analysis of the IVRS and MBA workshop**

An economic evaluation of the intervention package in improving successive health visits compared to the control group will be done. A cost-effectiveness analysis by assessing the balance between costs of the intervention and effects of improved visits from a healthcare provider perspective. Costs for all separate actions and time used by all individual health care professionals including the costs towards the workshop program, costs for the IVRS and all other materials. The costs involved in the intervention package and the benefits achieved compared with those of control arm will be estimated. With this data, we aim to perform a cost-effective analysis of the interventions after the 3.5-month follow-up.

Data Collection and storage: The research assistants will conduct and collect the interview with the help of an android application; MAASTHI- which was developed specifically for this project. The MAASTHI system aims to collect, validate, verify, and store the data of respondents, their follow-up, and their children. It is an integrated system that consists of a modular design at the core-system which ensures the utmost flexibility without compromising the operational strength. The system comprises a web front end and an Android app. The app is designed to work with the disconnected data model as well as a fully synchronous model. The system is designed with (Secure Sockets Layer) encryption with Secure Hash Algorithm 2 (SHA2). This ensures data privacy and protection. The system employs role-based authentication system. All the interview information will also be printed on paper and stored for documentation.

### Sample size

The current rate of screening is 77% for OGTT, and the expected rate is an increase of 10% through the interventions. In order to achieve 80% power to detect a small improvement of 10% in the screening with a significance level of 5% and 95% confidence interval, the required sample size is 50 in each arm after adding a non-response rate of 30%.

For the secondary objective, we have assumed that 50% will be followed-up at delivery. In order to achieve 80% power to detect a small improvement of 20% in follow up at delivery, with a two-sided significance level 95%, the sample size required in each arm is 104 persons [27, 28]. Assuming refusal and loss to follow up at 50%, the total number of women required per arm is 156 at delivery. Assuming higher loss to follow-up at 70% for following up children at 3 months of age, the required sample size in each arm is 265. Hence, we aim to recruit 265 pregnant women in each arm making a total of 795.

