MAASTHI is a prospective birth cohort with the aim of assessing the effects of glucose levels in pregnancy on the risk of adverse infant outcomes, especially in predicting the possible risk markers of later chronic diseases [18]. The recruitment of the pregnant women in MAASTHI began in April 2016. The current strategy deployed in MAASTHI cohort is to follow up pregnant women for Oral Glucose Tolerance Test (OGTT), at birth and in-person child assessments at 14 weeks, annually during the year 1, 2 and 3 of the child. Currently, we are recruiting around 80 pregnant women per month, with the completion of all their records, anthropometry measurements, and OGTT. Of the eligible pregnant women, only 77% completed OGTT despite offering the test free of cost and repeated reminders by the research team to get tested for gestational diabetes. Once the OGTT is done between 24 and 36 weeks of gestation, there is no further opportunity to meet them again until the delivery. The duration without contact increases the likelihood of attrition. In the intervening period of initial contact and follow-up’s, it is essential that the participants are continuously engaged by the research staff through innovative methods in order to attain better turn up rate for follow up. Despite stringent adherence of including only the residents of the source population, nearly 20% of the women did not attend the follow-up visits at birth. In order to prevent further loss to follow-ups in subsequent visits, we are interested in exploring whether interventions involving Interactive voice response system (IVRS) and conducting mother and baby workshops can improve follow-up rates.

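### The primary sample size of 50 per arm does not follow from its stated inputs: 77% versus 87% OGTT completion needs about 231 per arm before any allowance

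*Protocol article*

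**What the plan says.** The Sample size section of the protocol article sets out the primary calculation in two sentences. The first gives the rates: "The current rate of screening is 77% for OGTT, and the expected rate is an increase of 10% through the interventions". The second gives the target, "In order to achieve 80% power to detect a small improvement of 10% in the screening". It fixes alpha at 5% without saying whether the test is one- or two-sided, and concludes that "the required sample size is 50 in each arm after adding a non-response rate of 30" per cent. The Background reports the same control rate: "only 77% completed OGTT despite offering the test free of cost".

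The section then sizes the secondary outcomes. For follow-up at delivery it takes 50% with a gain of 20% and reaches 104 per arm. It raises this to 156 for 50% loss, and to 265 for 70% loss at the later child visit. Recruitment is set at 265 per arm, 795 in all. Study design specifies 1:1:1 allocation, and Statistical analysis specifies a chi-square comparison of the intervention groups with control.

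**The concern.** A gain of 10 points from 77% is modest, and a two-group comparison of proportions cannot usually detect it at 80% power with a few dozen women per arm. Fifty after a 30% allowance means only 35 to 38 evaluable women per arm.

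This is the only sample size justification for the primary outcome. A reader who sees 50 required and 265 recruited will conclude that OGTT completion has more than five times the women it needs, and may take a null result as firm evidence of no benefit. The same figure makes the secondary outcomes appear to drive recruitment with ample room to spare on the primary one. If 50 is wrong, both impressions are wrong too.

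**Working it through.** **Inputs** (Sample size section unless noted)

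- Control completion p1 = 0.77, also in the Background.
- Gain of 10%, read as absolute: p2 = 0.87, mean p = 0.82.
- Power 80% (z = 0.8416) and significance 5%. Sidedness is not stated for the primary outcome. The secondary calculation is run "with a two-sided significance level 95" per cent, so two-sided (z = 1.96) is the natural reading.
- Equal arms (Study design), chi-square test (Statistical analysis).

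**Step 1. Evaluable women implied by 50 per arm**

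50 × 0.7 = 35, or 50 / 1.3 = 38.

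**Step 2. Required number per arm before any allowance**

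n = [z(α/2)·√(2p(1−p)) + z(β)·√(p1(1−p1) + p2(1−p2))]² / (p2 − p1)²

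= [1.96·√(2 × 0.82 × 0.18) + 0.8416·√(0.1771 + 0.1131)]² / 0.10²

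= (1.0649 + 0.4534)² / 0.01 = 230.5, that is 231.

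The unpooled formula gives 228, and the continuity-corrected one about 250.

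**Step 3. Add the stated 30%**

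231 × 1.3 = 300, or 231 / 0.7 = 330. These are the figures to set beside the printed 50. The section's own later steps multiply (104 × 1.5 = 156; 156 × 1.7 = 265), so its convention points to about 300.

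**Step 4. Other readings**

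| Reading | Per arm, before allowance |
|---|---|
| Two-sided 5%, 77% vs 87% | 228 to 231 (about 250 with continuity correction) |
| One-sided 5%, 77% vs 87% | 180 to 182 (201 with continuity correction) |
| Two-sided 5%, relative 10% (77% vs 84.7%) | 409 |
| One-sample test of 87% against 77% | 95 (one-sided) to 123 (two-sided) |
| Single proportion to within ±10 points | 43 (at 87%) to 68 (at 77%) |

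The last row is not a power calculation, and after the allowance it gives 56 to 97. None of the readings yields 50 after the allowance.

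**Step 5. What 50 per arm can do**

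Power = Φ{[(p2 − p1)·√n − 1.96·√(2p(1−p))] / √(p1(1−p1) + p2(1−p2))}

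- n = 50: 25% (exact enumeration of the chi-square test: 26%).
- n = 38: 20%. n = 35: 19%.
- The difference detectable with 80% power at 35 to 38 per arm is 21 to 22 points, not 10.

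**Step 6. What the planned 265 per arm can do, each arm against control**

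| Condition | Power |
|---|---|
| All 265 counted, two-sided 5% | 85% |
| All 265 counted, 2.5% per comparison | 78% |
| 30% lost (about 185 left), two-sided 5% | 71% |
| 10% taken as relative, all 265 counted, two-sided 5% | 62% |

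Reaching 231 evaluable from 265 allows a loss of at most 1 − 231/265 = 13%.

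**Step 7. Cross-check on the secondary figure**

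50% vs 70%, two-sided 5%, 80% power, continuity-corrected, gives 103 against the stated 104. A standard formula with an absolute difference reproduces that number, so the primary figure is the one out of line.

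**The case against.** The strongest reply is that nobody recruits 50 per arm. The trial enrols 265, a number derived from the secondary outcomes, and at 265 the power for 77% versus 87% is 85%, above target. Correcting the 50 changes neither recruitment nor the test, so it can be called a reporting error. That is right about the trial's size, and the 19 to 25% power belongs to the printed figure, not to the trial. It does not make the printed figure correct. On the section's own inputs and multiplying convention, the primary outcome would need about 300 per arm and would set the sample size itself.

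The shortfalls also depend on assumptions. The 71% applies only if the 30% allowance is kept; once non-attendance counts as failure, it no longer applies. The 78% assumes a split of alpha that the article does not specify. The 62% assumes a relative gain, which the secondary calculation makes unlikely. A one-sided test needs about 182 per arm. If the two intervention groups were combined against control, about 168 controls would suffice and power at 265 per arm would be 94%. All of this stands as qualification. None of it produces 50: power at 50 is still only 36% one-sided, and 35% with the groups combined.

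Finally, the Outcome measures section divides by women due for OGTT within 36 weeks. Counting all randomised women is broadly compatible with that, but the denominator should be stated explicitly.

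**Conclusion.** The figure of 50 per arm is wrong as stated. With 77% versus 87%, two-sided 5%, 80% power and equal arms, about 231 per arm are needed before any allowance and 300 to 330 after 30%. No reading tested gives 50.

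The trial as planned is adequately but not generously sized for its primary outcome. Its 85% power per comparison rests on an absolute gain of 10 points, an unadjusted 5%, and every randomised woman being counted. This must be corrected, because it is the sole justification for the primary outcome and it misstates how much room the design has.

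**What to change.** In the Sample size section:

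- Delete the figure of 50 per arm.
- State that 77% versus 87%, as an absolute difference at two-sided 5% with 80% power, needs about 231 women per arm.
- State that the planned 265 per arm gives about 85% power for each comparison with control, or 78% if each is tested at 2.5%.
- Remove the 30% non-response allowance for this outcome, since failing to attend is the event being measured, and say that all randomised women are in the denominator, with no OGTT counted as not completed. Check that the response-rate definition under Outcome measures is worded to match.

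The total stays at 795. The cost is wording, mainly in this one section, and a less favourable but accurate statement of power. No extra women are needed.

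### The secondary-outcome calculation that sets 265 women per arm inflates for loss by the wrong formula, counts non-attendance as both outcome and loss, and rests on an unexplained 50% baseline

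*Protocol article*

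**What the plan says.** The Sample size section of the protocol article treats the primary outcome (OGTT completion) first and arrives at 50 women per arm. The recruitment target comes from the secondary objective instead.

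- Baseline: "For the secondary objective, we have assumed that 50% will be followed-up at delivery".
- Effect: the aim is "to detect a small improvement of 20% in follow up at delivery", with 80% power. The base figure is 104 per arm.
- First enlargement: "Assuming refusal and loss to follow up at 50%, the total number of women required per arm is 156 at delivery".
- Second enlargement: "Assuming higher loss to follow-up at 70% for following up children at 3 months of age, the required sample size in each arm is 265". The section then sets 265 per arm, 795 in total.

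The Secondary outcome measure section defines success as a completed delivery visit or a completed 3.5-month visit. The denominators are eligible live births and eligible 3.5-month-old infants. It defines loss to follow-up as the missed visits over essentially the same denominators.

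The Background reports, for the parent cohort, that "nearly 20% of the women did not attend the follow-up visits at birth".

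**The concern.** Three things in this chain do not fit together.

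1. An allowance for loss is made by dividing by the proportion retained. The printed figures come from multiplying by one plus the loss, which falls well short when losses are as large as 50% or 70%.
2. The event allowed for as loss is the event being measured. A woman who does not attend the delivery visit is an observed failure on that outcome. The 50% loss repeats the assumed 50% control follow-up rate.
3. The same cohort's reported attendance at birth is far from 50%, and no reason is given for the choice.

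The total of 795 rests on this chain, so the section does not tell a reader what the trial can detect at delivery or at 3.5 months. Treating non-attendance as loss also invites an analysis that drops non-attenders from the denominator, which would remove the outcome itself.

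**Working it through.** **Inputs.** From Sample size: control 50%, improvement 20%, power 80%, base n 104, losses 50% and 70%, final n 265. The significance level is printed as 95% two-sided and is read here as 5% two-sided. From Background: nearly 20% missed the birth visit. From Secondary outcome measure: the definitions of success and loss.

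**Base figure.** For two proportions, with p̄ the mean of p1 and p2:

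n = [1.96 √(2p̄(1−p̄)) + 0.84 √(p1(1−p1) + p2(1−p2))]² / (p1−p2)²

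With 0.50 and 0.70 this gives 93 per arm, or 103 with the continuity correction. The stated 104 is therefore sound, and the 20% is in percentage points. A relative reading (50% versus 60%) would need 388 to 408 per arm.

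**Inflation as printed.**

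- 104 x (1 + 0.5) = 156
- 156 x (1 + 0.7) = 265.2, i.e. 265

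Other routes do not give both figures: 104 x 1.7 = 177, 104/0.5 = 208, 104/0.3 = 347, 156/0.3 = 520.

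**Reading A: lost women are missing data.** To keep 104 evaluable, n = 104/(1−d).

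| Loss d | Needed per arm | Printed | Left from printed | Power, 50% vs 70% | With continuity correction |
|---|---|---|---|---|---|
| 50% | 208 | 156 | 156 x 0.5 = 78 | about 73% | about 67% |
| 70% | 347 | 265 | 265 x 0.3 = 79.5 | about 74% | about 68% |

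The last column uses the correction that leads to a base n of about 104.

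**Reading B: a missed visit is an outcome failure**, as the outcome definitions imply. No inflation for non-attendance is due, and 103 to 104 per arm is enough for 50% versus 70%. With 265 per arm in the denominator, power is 99.7%.

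**Baseline.** If nearly 20% missed the birth visit, about 80% attended. Adding 20 points to 80% gives 100%, which cannot serve as a target.

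**What 265 per arm detects** at 80% power, two-sided 5%, without continuity correction, if nearly all women stay in the denominator:

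| Control rate at delivery | Detectable difference |
|---|---|
| 80% | 8.8 points |
| 50% | 12.1 points |

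**3.5 months.** No control rate or target difference is stated for this visit. The 265 is the delivery calculation enlarged a second time.

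**The case against.** **The sample is large enough, so nothing is lost.** This largely stands. Readings A and B are alternatives and their shortfall and surplus cannot be added together. A reader might infer from Reading A that the trial is underpowered. The document does not support that: its own outcome definitions favour Reading B, under which 265 is ample for 50% versus 70%.

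**The two losses might be taken as successive**, leaving 15% of women and much lower power. The text does not say this. It states 70% loss at 3 months; the compounding appears only in the multiplication.

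**Some inflation is legitimate.** This stands. The 50% covers refusal as well as loss, and women without an eligible live birth or infant leave the denominator without being failures. It would go too far to say that no allowance is due, or that every randomised woman belongs in the denominator. The text does not separate these causes from non-attendance.

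**The 50% is a planning assumption, not a contradiction.** This stands in part. The Background gives no denominator for its 20%, and success in the trial is stricter: questionnaire and anthropometry within one week of delivery. The Background also cites losses of 14 to 82% in Indian cohorts, a range that contains 50%. A strict contradiction is therefore not shown. What remains is that 50% is unexplained beside the cohort's own figure, although the same section uses the cohort's observed 77% for OGTT.

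**Only secondary outcomes are affected.** This stands and lowers the severity.

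**Conclusion.** The derivation of 265 per arm is wrong as written. On its own treatment of loss, the printed number gives about 74% power (about 68% with continuity correction) instead of 80%; 347 per arm would be needed at 70% loss. On the protocol's own outcome definitions, the inflation for non-attendance should not be there, and 265 gives over 99% power for 50% versus 70%. The errors pull in opposite directions, so the finding is a faulty derivation and not a sample that is too small.

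The delivery baseline needs a reason: against about 80% attendance, a 20-point gain is at the ceiling. That part depends on the Background figure applying to a comparable group and a comparable definition of attendance, which the document does not settle.

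The power figures assume a two-sided 5% test of one intervention arm against control, with 20% read as percentage points. The point ranks below a must-fix: it concerns secondary outcomes and the number recruited does not change.

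**What to change.** Keep 795 women and rewrite the secondary-outcome part of the Sample size section:

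1. Remove the 50% and 70% enlargements for non-attendance. State that a missed visit counts as failure among the denominators already defined: eligible live births and eligible 3.5-month-old infants.
2. Make an allowance only for refusal and for women who leave those denominators. State each proportion d and divide by (1−d).
3. Justify the delivery baseline against the cohort's observed attendance, giving the denominator of the 20% in the Background. If 50% is kept because the trial's definition of success is stricter, say so.
4. Replace the 20-point target with what 265 per arm detects at 80% power: for example about 9 points from 80%, or about 12 points from 50%, if nearly all women remain in the denominator. Recalculate with the reduced n if step 2 removes many.
5. State a control rate and a detectable difference for the 3.5-month visit, which currently has neither.
6. Print the significance level as 5%.

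The cost is a rewritten paragraph and a short recalculation. No additional women and no change in conduct are needed.

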### Statistical analysis

Descriptive statistics of participants’ baseline characteristics will be presented to assess their comparability. These statistics will be reported as a mean (SD) or median (first quartile, third quartile) for continuous variables, and count (per cent) for categorical variables. Baseline characteristics will include age, education, occupation, income, parity, gestational age, and mobile phone access. We calculate the response rate for OGTT in each of the study arms. For the primary analysis, we will compare the proportion of participants retained during the eligible period in the MBA and IVRS group with those in the control group using a Chi-square test.

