**Discussion:**

Between the two interventions (IVR and MBA), the study results would uncover the contextually specific, timely intervention, which can increase the proportion of pregnant women followed up in public hospitals. If effective, this study will provide information on an effective intervention, useful in ensuring the success of longitudinal follow-up in the public hospitals.

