##### Mother and baby affairs (MBA) workshops:

This arm of intervention will involve antenatal workshop and counselling for parents. This will include organizing a lunch for the participant and her family (husband and kids if any). Generally, this is called as “Seemantha” in Kannada similar to “Godhbharai” in northern India and baby shower in other parts of the world. However, the intervention will involve particular components. Such asA brief talk by health professionals on importance of GDM screening and management and other antenatal and postnatal topics.A health-related quiz competition followed by gifts distribution to winners andRole-plays on personal hygiene, the importance of having nutritional food, delivering at the hospital, precautions at the time of delivery, caring for the baby, feeding of colostrum, homemade baby food, immunization, and family planning measures.

Conducted ahead of OGTT, this activity will be done every month in batches for around 25 participants. We will also ensure father’s participation in the program for increased engagement in managing the health of mother and child. Anganwadi Worker (AWW) and Accredited Social Health Activist (ASHA) workers will also be involved.

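### The named Chi-square test ignores the MBA workshop batches, and a comparison with control alone cannot support the promised choice between IVRS and MBA

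*Protocol article*

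**What the plan says.** - **Primary analysis** (Protocol article, Statistical analysis). The only method named compares the proportion retained "in the MBA and IVRS group with those in the control group using a Chi-square test". The section mentions neither workshop batches nor an IVRS-MBA contrast.
- **Delivery of MBA** (Mother and baby affairs workshops). Of the workshop the article says "this activity will be done every month in batches for around 25 participants". Theoretical background says this arm works through peer pressure and discussion of shared goals.
- **Allocation** (Study design). Women are randomized individually, 1:1:1.
- **Aim** (Abstract, Discussion). "Between the two interventions (IVR and MBA), the study results would uncover the contextually specific, timely intervention". The abstract's Methods describe the outcome as a difference among three arms. The primary objective in the main Methods is the effectiveness of the two interventions.
- **Planning values** (Sample size). "The current rate of screening is 77% for OGTT, and the expected rate is an increase of 10% through the interventions", "with a significance level of 5% and 95% confidence interval". The trial will recruit 265 women per arm.

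**The concern.** Two features of the design do not fit the named test.

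First, women in one MBA workshop share a session, speakers and discussion, and the article expects them to influence one another. Individual randomization does not remove correlation that arises after allocation. If OGTT attendance varies from batch to batch, the MBA proportion has a larger variance than the binomial one that the Chi-square test assumes. The standard error is then too small, the interval too narrow and the test anti-conservative.

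Second, the article promises to identify an intervention from the two, but the named comparison is with control. If one arm is significant against control and the other is not, that does not show that the first beats the second. A hospital choosing on that pattern could choose on chance.

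A further question is which contrasts are primary. If the sentence means two separate 5% tests, the chance of at least one false positive exceeds 5% even without clustering.

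**Working it through.** **Inputs.** From the article: 265 women per arm; batches of about 25, so 265/25 = 10.6, or about 11 batches; 77% OGTT completion under control, rising by 10 points to 87% (absolute reading); 5% level, taken as two-sided (critical value 1.96). The ICC is assumed at 0.01, 0.02 and 0.05.

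**The plan's own figure.** Sample size states 80% power for the primary outcome. At the planned 265 per arm with complete data, the unclustered two-sided test of 77% against 87% has about 85% power. That is the baseline here. The article's separate figure of 50 per arm for this outcome is a different matter and is not used.

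**Step 1: size of the MBA-control test.** The design effect is DE = 1 + (25 − 1) × ICC. Only the MBA arm is inflated, so under no difference the true variance of the contrast is (1 + DE)/2 times the assumed one. True size = 2 × [1 − Φ(1.96/√((1 + DE)/2))].

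| ICC | DE | √((1+DE)/2) | 1.96 divided by it | True size |
|---|---|---|---|---|
| 0 | 1.00 | 1.000 | 1.960 | 5.0% |
| 0.01 | 1.24 | 1.058 | 1.852 | 6.4% |
| 0.02 | 1.48 | 1.114 | 1.760 | 7.8% |
| 0.05 | 2.20 | 1.265 | 1.549 | 12.1% |

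Simulation with beta-binomial batches (ten of 25 and one of 15) at 77% gave 6.5%, 7.8% and 12.0% for the three non-zero ICCs.

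**Step 2: can tests against control choose between interventions?** Let both interventions truly reach 87% against 77%, with 265 per arm and no clustering. In simulation each arm was significant against control in about 85.5% of trials, both in 76.6%, neither in 5.6% and exactly one in 17.8%. So in about 18% of trials one of two equally effective interventions would look like the only one that works.

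**Step 3: if two separate 5% tests are meant.** The two contrasts share the control arm (correlation 0.5 without clustering). A bivariate normal calculation, with the MBA variance inflated as in step 1, gives the chance of at least one false positive. A single three-arm (3×2) test, simulated, is shown beside it.

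| ICC | Two tests against control | One 3×2 test |
|---|---|---|
| 0 | 9.1% | 5.1% |
| 0.01 | 10.4% | 6.4% |
| 0.02 | 11.8% | 7.6% |
| 0.05 | 15.9% | 11.7% |

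**Step 4: what an honest variance costs.** SE = √[(0.77 × 0.23 + DE × 0.87 × 0.13)/265], and power = Φ(0.10/SE − 1.96).

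| ICC | SE | Power | 95% half-width |
|---|---|---|---|
| 0 | 0.0331 | 86% | 6.5 points |
| 0.01 | 0.0346 | 82% | 6.8 points |
| 0.02 | 0.0361 | 79% | 7.1 points |
| 0.05 | 0.0401 | 70% | 7.9 points |

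The 86% at ICC 0 and the 85% baseline differ only because this formula does not pool the variance.

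**The case against.** The case against has several parts.

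- **Two uncorrected tests.** A reader might infer that the plan runs two uncorrected 5% tests. The sentence does not say so. It names one Chi-square test and no level, and the abstract speaks of three arms, so a single 3×2 test fits and holds about 5% without clustering. The article is also a condensed account, and multiplicity rules are commonly left to an analysis plan. This stands.
- **Familywise control.** The article would offer control women whichever interventions succeed. That can be read as a separate decision on each intervention, with each one entitled to its own 5%. Whether familywise control is needed is therefore debatable. This stands too.
- **A false-positive risk of 9–16%.** A reader might quote this range as a property of the plan. It is not. The lower end needs the two-test reading and the upper end needs an ICC of 0.05 as well. The documents give no ICC, and the inflation also requires batches to differ when the workshop has no average effect.
- **The head-to-head aim.** It rests mainly on one sentence in the abstract, while the formal objective can be met by comparisons with control. Nothing says that the arm with the smaller p-value will be chosen, and an unseen plan may contain an IVRS-MBA contrast. So one cannot say that the trial never compares them, only that the primary comparison the article names does not.

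None of this removes the core. Neither reading of the sentence allows for batches, and correcting for them means departing from the plain Chi-square test that the article fixes. Nor does either reading, on its own, deliver the stated choice between interventions.

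**Conclusion.** The point holds in a conditional form. The named test treats women taught in about 11 shared workshops as independent. If batches differ in attendance, the MBA-control test is anti-conservative: 6.4%, 7.8% or 12.1% instead of 5% at an assumed ICC of 0.01, 0.02 or 0.05. These figures rest on full batches of 25 and on batch variation that exists without an average workshop effect.

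The named comparison with control also cannot support the choice in the abstract. With two equally effective interventions at the planning values, about 18% of trials would show exactly one as significant.

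The multiplicity figure (about 9% at ICC 0, and about 10%, 12% or 16% at the three ICCs) applies only if two separate 5% tests are meant. On that, the documents support a request for clarity and not a finding of error.

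**What to change.** 1. **Record the batch.** Store each MBA woman's workshop batch while the workshops are running. This is one data field.
2. **Replace the plain Chi-square test.** Use a binomial risk-difference analysis in which every test and every confidence interval uses batch-robust standard errors, with each MBA batch as a cluster and all other women as singletons. A small-sample correction is essential with about 11 batches. In simulation, a robust global test with only an 11/10 scaling still had a size of about 6–7%.
3. **Match the conclusion to the contrasts.** State which contrasts are primary. Either add the IVRS-MBA risk difference with its confidence interval, or limit the conclusion to each intervention against control.
4. **Optional familywise control.** A global three-arm test at 5%, followed by pairwise 5% tests only if it is significant, controls the familywise error for three arms, provided that the global test is batch-robust as well.

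**Cost.** Arms and recruitment do not change. MBA-control power for 77% against 87% at 265 per arm falls from about 86% at ICC 0 to about 82%, 79% or 70% at ICC 0.01, 0.02 or 0.05, before attrition and before any small-sample or multiplicity correction, and the MBA interval widens as in step 4. With the optional closed procedure in batch-robust form, simulated MBA power was about 78%, 74% and 64%.
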